## Recruitment

Recruitment will take place over a 2 month period (8 weeks). Inactive patients fulfilling the inclusion criteria will be provided with a participant information sheet about the study by the project officers and a subset of patients (40%) showing interest will be offered an accelerometer to be worn for a week prior to their measurement visits to validate the GPAQ results and as a primary measurement tool to evaluate the change in METS-mins/week, sitting time and step counts. Initially all participants (*n* = 220) will be offered accelerometers until the required numbers are reached in all eight health center (*n* = 11). Subsequently, an appointment will be given to all potential participants to attend a wellbeing clinic for baseline measures, linked to their diabetes clinic, within a week. A telephone call will be made to all willing participants to remind them of their appointment and ensure activation of the accelerometer.

At the baseline visit the project officers will seek written informed consent and log any eligible individuals who decline participation (Fig. 1).

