**Methods/design:**

The study is a one year 1:1 cluster randomized controlled trial of the MOVEdiabetes programme (intervention) versus usual care in eight primary health care centres in Oman. The MOVEdiabetes programme utilizes face to face physical activity consultations promoting 150 min of moderate to vigorous physical activity per week (≥600MET-mins/week), pedometers to self-monitor step counts and monthly telephone WhatsApp messages for follow up support. Inactive adults with type 2 diabetes and no contraindication to physical activity will be recruited over a two months period, and followed up for 12 months. To demonstrate a 50% between group difference in physical activity levels (MET-mins/week) over 12 months, (at a power of 80%, and significance level of 5%), 128 participants would be required to complete the study (64 in each arm). Based on a drop-out rate of 20%, 154 participants would require to be recruited (77 in each arm). Assuming a recruitment rate of 70%, 220 potential eligible participants would need to be approached. The primary outcome is change in levels of physical activity measured by the Global Physical Activity Questionnaire. In addition, accelerometers will be used in a sub group to objectively assess physical activity. Secondary outcomes include changes in metabolic and cardiovascular biomarkers, change in self-reported health, social support, self-efficacy for physical activity, and perceived acceptability of the program. All intervention delivery and support costs will be monitored.

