## Measures/assessment instruments

Baseline and follow-up data will be collected face to face and from the electronic health information system in the health centre (AlShifa system) (Table 1).

**Table 1 Tab1:** Outcome measures

	Tool	When	
		Intervention	Comparison
Primary outcome			
GPAQ-MET-mins/week	Questionnaire	B, 3 F, 12 F	B, 3 F, 12 F
Accelerometer (activePAL^TM^)	Reporting step count, MET-min/week, and sitting time	B, 3 F, 12 F	B, 3 F, 12 F
Pedometer (YAMAX Digi-walker SW-200)	Reporting step counts	B, 3 F, 12 F	-
Secondary outcomes			
Socio-demographic data	Questionnaire	B	B
Height (m)	Stadiometer	B	B
Body weight (Kg)	Calibrated scales	B, 3 F, 12 F	B, 3 F, 12 F
Waist circumference (cm)	Tape measure	B, 3 F, 12 F	B, 3 F, 12 F
Lipid profile (mmol/l)	Blood test (venous fasted sample)	B, 3 F, 12 F	B, 3 F, 12 F
Blood pressure (mmHg)	Sphygmomanometer	B, 3 F, 12 F	B, 3 F, 12 F
^a^HbA1c (%)	Blood test (fasted sample)	B, 3 F, 12 F	B, 3 F, 12 F
Self-assessed general health	Questionnaire	B, 3 F, 12 F	B, 3 F, 12 F
Self-efficacy for PA	Questionnaire	B, 3 F, 12 F	B, 3 F, 12 F
Social support for exercise	Questionnaire	B, 3 F, 12 F	B, 3 F, 12 F
Cost analysis (description)	Detailed cost description	12 F	-
Exit survey	Questionnaire (participants and project officers)	12 F	-

(B = baseline; 3 F = 3 month follow-up, 12 F = 12 month follow-up)

^a^while blood collection for HbA1c at 12 month is mandatory, it is only done at baseline and 3 month if missing from the electronic health information system or recorded within more than 4 months prior to the measurement visits

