### Pedometer

Participants will be given a pedometer (YAMAX Digi-walker SW-200) at their baseline visit. Instructions on how to use the pedometer, how to record their daily steps and how to set daily step goals will be discussed by the project officers. Participants will be asked to set individual goals and fill in a daily step count to be submitted to the project officers in their respective health centres over a three month period and at 12 months.

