## Statistical analysis

The initial quantitative analysis will be an intention-to-treat analysis between the two cluster groups (intervention versus control) but secondary analyses will explore the effect of actual treatment received. The initial analysis will involve standard two-sample comparisons (parametric or nonparametric as dictated by the distribution of the data) looking at effect sizes at 3 and 12 months using t-tests or Mann-Whitney tests for differences in means as well as repeated measures or chi squared tests for differences in proportions. Differences by health centre will be explored and, if statistically significant will be entered in a mixed model as a random effect. The balance of characteristics between treatment and control arms will be tabulated and if differences are noted, adjustment will be made for these in linear regression models.

Results from the open-ended questions in the exit survey will be analysed thematically to identify the perceived acceptability of the intervention (content, delivery and aims) to the participants and project officers (health care providers).

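### Table 1 and the Recruitment section give primary status to the accelerometer, and Table 1 to the pedometer, contradicting the single GPAQ primary outcome of the abstract; no primary time point is named

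*Protocol article*

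**What the plan says.** The protocol article describes its primary outcome in several places.

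- **Abstract, Methods/design:** "The primary outcome is change in levels of physical activity measured by the Global Physical Activity Questionnaire". The accelerometer is brought in separately: "In addition, accelerometers will be used in a sub group to objectively assess physical activity". No time point is attached to the primary outcome.
- **Sample size:** one quantity, MET-mins/week, over 12 months, with 80% power and a single 5% level. It requires 128 completers, 64 per arm.
- **Recruitment (accelerometer paragraph):** the accelerometer goes to a 40% subset. It is to validate the GPAQ and also serve "as a primary measurement tool to evaluate the change in METS-mins/week, sitting time and step counts".
- **Measures/assessment instruments, Table 1:** the block of primary outcomes has three rows. The first is "GPAQ-MET-mins/week". The second is the accelerometer, described as "Reporting step count, MET-min/week, and sitting time". The third is "Pedometer (YAMAX Digi-walker SW-200"), giving step counts. All three are scheduled at baseline, 3 and 12 months. The pedometer row has a dash for the comparison arm.
- **Intervention, Pedometer:** the pedometer is an intervention component. "Participants will be given a pedometer (YAMAX Digi-walker SW-200) at their baseline visit".
- **Statistical analysis:** two-sample comparisons between the arms, "looking at effect sizes at 3 and 12 months". Neither time is called primary.

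**The concern.** The primary endpoint decides what the trial may conclude, and here its definition depends on which section is read. The abstract has one instrument. Table 1 has three, covering five quantities: one from GPAQ, three from the accelerometer and one from the pedometer. Two follow-up times are then analysed without ranking.

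Disagreement between these candidates is plausible. GPAQ is self-reported and the accelerometer is objective. The face-to-face consultations end at week 8, so a 3-month gain could fade by 12 months. As the document stands, an author could point to text supporting primary status for whichever result was favourable.

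The pedometer row is a separate fault. With no comparison-arm data it can give only a before-after change in the intervention arm, measured with a device that is itself part of the intervention. That is not an outcome of a randomised comparison.

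**Working it through.** **1. What the sample size assumes.** Inputs from the Sample size section: 80% power, 5% level, 64 per arm. The section states a 50% difference but gives no mean or SD, and no sidedness. Assumption: 50% is read as 0.5 SD, two-sided.

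- Normal formula: n per arm = 2 × (1.960 + 0.842)² / 0.5² = 2 × 7.85 / 0.25 = 62.8, so 63.
- The t-test version gives 63.8, so 64 per arm and 128 in all. Power at 64 per arm is 0.801.
- A one-sided test would need 50 per arm and does not match.

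On this reading the plan's figure reproduces as one two-sided comparison at 5%. Bonferroni sharing of the 5% would need 78 per arm for two tests, 91 for four and 105 for eight, so 64 leaves no room for several primary tests.

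**2. How many between-arm tests the primary labels allow.** The pedometer adds none, because it has no comparison arm.

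- GPAQ alone at two times: 2 tests.
- GPAQ and accelerometer MET-mins at two times: 4 tests.
- GPAQ and all three accelerometer quantities at two times: 8 tests.

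**3. Chance of at least one false positive**, if each test were judged at an unadjusted 5%. Under independence this is 1 − 0.95^k. The correlated values come from simulated test statistics with equal pairwise correlation.

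| Tests | Independent | Correlation 0.5 | Correlation 0.9 |
|---|---|---|---|
| 2 | 0.0975 | 0.091 | 0.070 |
| 4 | 0.185 | 0.155 | 0.093 |
| 8 | 0.337 | 0.249 | 0.118 |

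For four tests the values at correlations 0.3 and 0.7 are 0.174 and 0.130. The documents give no correlation, so the range 0.093 to 0.185 is the honest statement for that case.

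**4. Power of the accelerometer subset.** Inputs from the Recruitment section: 40%, and 11 in each of eight centres. 11 × 8 = 88 = 40% of 220, or 44 per arm. The text does not settle whether these are devices worn or offered, or whether the 40% applies to those approached or to those recruited. Assumption: 0.5 SD, two-sided 5%, no clustering.

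| Reading | Per arm | Power |
|---|---|---|
| 11 per centre attained | 44 | 0.64 |
| Same, after 20% dropout | 44 × 0.8 = 35.2 | 0.54 |
| 40% of the 154 recruited | 154 × 0.4 / 2 = 30.8 | 0.49 |
| Same, after 20% dropout | 30.8 × 0.8 = 24.6 | 0.41 |

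Taking 70% uptake of 88 offers gives the same 61.6 people as 40% of 154, so that reading falls in the lower two rows. Randomisation is by centre, so all these powers are upper bounds.

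**The case against.** The strongest reply is that the primary endpoint is not really in doubt. The abstract names GPAQ alone and sets the accelerometer apart. The sample size uses MET-mins/week over 12 months, and the consultation section sets its activity goal for 12 months. GPAQ is collected in both arms at both times. This stands. A reader might infer from Table 1 that the trial has no valid primary test, but the documents do not support that: GPAQ MET-mins/week at 12 months is a valid between-arm test and is the one the abstract and sample size point to.

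A reader might also infer that the plan tests every measure at both times at 5%. It does not say so. The 5% appears only with the sample size, and the Statistical analysis section gives no level per test. The error rates above are therefore conditional. Rules for multiplicity, or for disagreement between instruments, may properly sit in a statistical analysis plan, so their absence is not part of this point.

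Table 1 is also loosely headed: its secondary block includes height and socio-demographic data, taken only at baseline. It may be a list of instruments by topic rather than a list of confirmatory tests. That weakens it as evidence of intent. It does not explain the Recruitment wording, which separately calls the accelerometer primary.

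The pedometer cannot enter the planned analysis, which compares the two arms, so its harm is limited to a misleading label. Its baseline reading can stay as a reference for the step increases the intervention encourages.

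Finally, quoting only 41% power for the accelerometer would pick the low end of a range that reaches 0.64.

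What survives is the conflict between labels. A separate analysis plan cannot resolve it silently, because any choice would contradict part of this document.

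**Conclusion.** The document is wrong as written, but in a limited way. One primary endpoint, GPAQ MET-mins/week over 12 months, can be recovered from the abstract and the sample size. Table 1 and the Recruitment section contradict it by promoting the accelerometer, and Table 1 does the same for a pedometer that has no control data. The Statistical analysis section does not choose between 3 and 12 months.

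If GPAQ and accelerometer MET-mins at both times were each treated as primary without adjustment, the false-positive chance would be about 9% to 18.5% instead of 5%, for correlations from 0.9 down to zero. The accelerometer subset would have about 0.41 to 0.64 power, given 0.5 SD and no clustering, so it is poorly suited to a primary role on any reading of its size. Both 0.5 SD for GPAQ and its transfer to the accelerometer are assumptions. The contradiction in the text depends on none of these figures.

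**What to change.** - In Table 1 and the Statistical analysis section, state GPAQ MET-mins/week at 12 months as the sole primary endpoint.
- Make GPAQ at 3 months and all accelerometer quantities at both times secondary, in Table 1 and in the analysis text.
- In the Recruitment section, delete the wording that makes the accelerometer a primary tool and keep its validation role.
- In Table 1, move the pedometer row out of the primary block and label it an intervention-arm process or adherence measure. Its time points can stay.

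This changes wording only. Data collection is untouched, and this point requires no change to the 64 per arm, which already matches a single primary comparison under the 0.5 SD reading. The cost is that accelerometer and 3-month findings can be claimed only as secondary, even if they are the more favourable results.

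### Accelerometers are worn for the baseline week, and the quota of 11 per centre is filled, before written consent is sought

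*Protocol article*

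**What the plan says.** The protocol article has two sections headed Recruitment. The second, after the exclusion criteria, sets out the order of events.

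- Inactive patients who fulfil the criteria receive an information sheet, and "a subset of patients (40%) showing interest will be offered an accelerometer to be worn for a week prior to their measurement visits".
- The device data serve "to validate the GPAQ results and as a primary measurement tool to evaluate the change in METS-mins/week, sitting time and step counts".
- The quota is described as follows: "Initially all participants (*n* = 220) will be offered accelerometers until the required numbers are reached in all eight health center (*n* = 11").
- Patients are then given a baseline appointment and telephoned to "remind them of their appointment and ensure activation of the accelerometer".
- Consent comes last: "At the baseline visit the project officers will seek written informed consent and log any eligible individuals who decline participation".

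Table 1 (Measures/assessment instruments) lists the accelerometer under the primary outcome, with values at baseline, 3 months and 12 months in both arms. The footnote to Table 2 and the section on face-to-face consultations both put seven days of recording before the week 0 consultation in the accelerometer subgroup.

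**The concern.** The baseline wear week is a research procedure. It is not part of eligibility screening, for which the protocol uses the Scot-PASQ. Its product is a baseline outcome value. On the stated order, that value is recorded from people who have not yet given written consent, and some of them are expected to decline, since the same sentence provides for logging decliners.

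Two things are at stake. One is ethical and administrative: the trial would hold recordings from people who never gave written consent, and the article does not say what becomes of them. The other is the size of the accelerometer subset. If the 11 places per centre are taken up before consent, each wearer who declines removes one person from the subset, and no rule for reissuing the device is given.

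**Working it through.** **Order of steps.** Taken together, the statements in Recruitment give: information sheet, device offer, appointment, activation call, a week of wear, baseline visit, written consent or refusal. The wear is tied to the period before the measurement visit ("will be offered an accelerometer to be worn for a week prior to their measurement visits"), and the activation call precedes the appointment. Consent is tied to the visit itself. The text describes no other consent step.

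**Inputs.**

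| Input | Value | Source |
|---|---|---|
| Devices per centre, number of centres | 11, 8 | Recruitment |
| Accelerometer fraction | 40% | Recruitment |
| Number approached | 220 | Recruitment; Sample size |
| Number recruited | 154 | Sample size |
| Recruitment rate, approach to enrolment | 70% | Sample size |
| Consent rate among wearers, c | not given; 70% to 90% assumed | assumption |

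**Reproducing the quota.**

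- 11 × 8 = 88.
- 40% of those approached: 0.40 × 220 = 88, an exact match.
- 40% of those recruited: 0.40 × 154 = 61.6, no match.
- Recruitment chain: 154 / 0.70 = 220, as stated.

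The quota of 88 is therefore 40% of the people approached, who have not yet consented.

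**Places lost if the 88 are filled before consent.** Consented wearers = 88 × c; places lost = 88 × (1 − c).

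| c | Consented wearers | Per centre | Places lost |
|---|---|---|---|
| 0.70 | 61.6 | 7.7 | 26.4 |
| 0.80 | 70.4 | 8.8 | 17.6 |
| 0.90 | 79.2 | 9.9 | 8.8 |

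**Did the planners allow for this?** 88 × 0.70 = 61.6, which is also 40% of 154. The 40% thus holds among those approached and, if wearers consent at the overall rate, among those recruited. About 62 enrolled wearers may be what was intended. In that case there is no shortfall against plan, but the plan would then expect about 26 people to be recorded who never give written consent.

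**The case against.** The strongest reply is that wearers are not a cold sample. They have had the information sheet, shown interest and accepted a device. The inclusion criteria also require willingness to give written consent. The 70% in Sample size covers every refusal between approach and enrolment, many of which would come before a device is offered, so applying it to wearers probably overstates the loss. Nor does the article say whether the 11 counts people offered, accepting or consented. Seeking a signature some days after the information sheet has a sound purpose, because it gives time to reflect. All of this stands, and it limits the size of the point. It does not change the stated order.

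A reader might go further in three ways that the article does not support.

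- **That wearers have not agreed at all.** Verbal agreement is plausible. What is missing during the wear week is written consent, the only kind the text describes. The consent sentence refers to the participant flow chart (Fig. 1), which was not available for this check.
- **That moving consent would bring a definite gain in power.** The article gives no standard deviation, effect size or power target for the subset. Any such figure would rest on an assumed effect, and one that ignored the eight clusters would be flattering.
- **That declining after wear will differ by arm because allocation is known.** The Randomisation section says centres are told their allocation but not when, relative to recruitment. If it is known by the baseline visit, it may equally be known at first contact, so moving the form would not remove the selection.

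**Conclusion.** The point holds as a matter of sequence. As written, a research-only baseline measurement, listed under the primary outcome, is made before written consent is sought, and the accelerometer quota is filled from people who can still decline. This is a stated order of steps, not detail left to a fuller document.

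The size is modest and uncertain: about 26 to 9 of 88 places, on an assumed consent rate of 70% to 90% among wearers, with no reissue of devices. The upper end is an illustration, for the reasons given above. The abstract names the GPAQ as the primary outcome measure and places accelerometers in a subgroup, and the 128/154/220 calculation does not depend on this point. The consent timing needs correcting whatever the number of decliners.

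**What to change.** Amend Recruitment so that written consent is sought before any accelerometer is issued and activated. Count the 11 per centre among consented participants only, and keep the other baseline measures at the baseline visit.

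The change means a longer first contact and less time to reflect after the information sheet. It may also mean more device fittings at 3 and 12 months, since more of the 88 would be enrolled participants. With all 88 consented, the subset would be 88 / 154 = 57% of those recruited, so the text should also say which group the 40% refers to. If 40% of those recruited was meant, the matching count is 61.6 / 8 = 7.7, or about 8 consented participants per centre.

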**Fig. 1 Fig1:**
[figure not shown]
Participants flow chart

Recruitment will be monitored fortnightly and efforts to reduce loss to follow-up will be made. Participants not attending their appointment will be called to consider rescheduling their appointments. Reasonable travel costs will be reimbursed.

## Measures/assessment instruments

Baseline and follow-up data will be collected face to face and from the electronic health information system in the health centre (AlShifa system) (Table 1).

**Table 1 Tab1:** Outcome measures

	Tool	When	
		Intervention	Comparison
Primary outcome			
GPAQ-MET-mins/week	Questionnaire	B, 3 F, 12 F	B, 3 F, 12 F
Accelerometer (activePAL^TM^)	Reporting step count, MET-min/week, and sitting time	B, 3 F, 12 F	B, 3 F, 12 F
Pedometer (YAMAX Digi-walker SW-200)	Reporting step counts	B, 3 F, 12 F	-
Secondary outcomes			
Socio-demographic data	Questionnaire	B	B
Height (m)	Stadiometer	B	B
Body weight (Kg)	Calibrated scales	B, 3 F, 12 F	B, 3 F, 12 F
Waist circumference (cm)	Tape measure	B, 3 F, 12 F	B, 3 F, 12 F
Lipid profile (mmol/l)	Blood test (venous fasted sample)	B, 3 F, 12 F	B, 3 F, 12 F
Blood pressure (mmHg)	Sphygmomanometer	B, 3 F, 12 F	B, 3 F, 12 F
^a^HbA1c (%)	Blood test (fasted sample)	B, 3 F, 12 F	B, 3 F, 12 F
Self-assessed general health	Questionnaire	B, 3 F, 12 F	B, 3 F, 12 F
Self-efficacy for PA	Questionnaire	B, 3 F, 12 F	B, 3 F, 12 F
Social support for exercise	Questionnaire	B, 3 F, 12 F	B, 3 F, 12 F
Cost analysis (description)	Detailed cost description	12 F	-
Exit survey	Questionnaire (participants and project officers)	12 F	-

(B = baseline; 3 F = 3 month follow-up, 12 F = 12 month follow-up)

^a^while blood collection for HbA1c at 12 month is mandatory, it is only done at baseline and 3 month if missing from the electronic health information system or recorded within more than 4 months prior to the measurement visits

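### The 4-month look-back for HbA1c permits a result from at or before baseline to count as the 3-month outcome, which can dilute the 3-month comparison

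*Protocol article*

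**What the plan says.** All references are to the protocol article.

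- **Schedule.** Table 1 (Measures/assessment instruments) lists HbA1c as a secondary outcome in both arms at all three time points: "B = baseline; 3 F = 3 month follow-up, 12 F = 12 month follow-up".
- **Data source.** The text above the table says: "Baseline and follow-up data will be collected face to face and from the electronic health information system in the health centre".
- **Draw rule.** Footnote a fixes when blood is taken for HbA1c. A fresh sample is required at the end: "while blood collection for HbA1c at 12 month is mandatory". For the two earlier visits, "it is only done at baseline and 3 month if missing from the electronic health information system or recorded within more than 4 months". The look-back is counted from each visit: "recorded within more than 4 months prior to the measurement visits".
- **Lipids.** The row "Lipid profile (mmol/l") is a fasting venous sample at the same three time points in both arms. It carries no footnote allowing a record value instead.
- **Analysis.** The abstract states: "Secondary outcomes include changes in metabolic and cardiovascular biomarkers". Statistical analysis plans between-arm comparisons "looking at effect sizes at 3 and 12 months using t-tests or Mann-Whitney tests for differences in means".

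Nothing in the article requires the 3-month HbA1c to be dated after baseline, or to be a different result from the one used as baseline.

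**The concern.** One look-back serves two visits that lie closer together than the look-back is long. At baseline this does no such harm, because any value up to 4 months old precedes the intervention, as a baseline value should. At 3 months the same allowance reaches back past the start of the intervention, so the rule can fill the follow-up cell with a value that contains no follow-up.

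At stake is the early HbA1c result. The face-to-face consultations take place at weeks 0, 4 and 8, so 3 months is the HbA1c time point that comes soon after them. Pre-intervention values entered there would make an early effect look smaller than it is. An analysis plan written later could exclude such values, but it could not recover samples that were never drawn.

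**Working it through.** The plan states no figure for this point, so there is none to reproduce. The check is date arithmetic on the footnote, followed by the size of the dilution.

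**1. Accepted windows, in months from baseline**

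Inputs from Table 1 and footnote a: visits at 0 and 3; look-back 4.

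- Baseline value: from 0 - 4 = -4 up to 0.
- 3-month value: from 3 - 4 = -1 up to +3.
- Overlap: -1 to 0, that is 1 month. If the visit falls at week 12, the window opens at 12 - 4 x 52/12 = -5.3 weeks, so the overlap is about 5 weeks.

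**2. What the rule does, by the record at baseline**

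Assume that no newer routine result appears before the 3-month visit and that samples drawn for the trial are entered in the electronic record. The article states neither.

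| Latest record value at baseline | Draw at baseline? | Age of latest value at 3 months | Draw at 3 months? |
|---|---|---|---|
| Missing, or older than 4 months | Yes | 3 months (the baseline draw) | No |
| 1 month old or less | No | 3 to 4 months | No |
| More than 1 and up to 4 months old | No | more than 4, up to 7 months | Yes |

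In the first two rows one result serves both visits and the change is exactly 0. The rule thus waives the follow-up draw for the participants whose baseline value is freshest.

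**3. Values dated after baseline**

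Any routine value from month 0 to +3 also qualifies. One taken in the first four weeks precedes the consultations at weeks 4 and 8, so it reflects only part of the intended exposure. The dilution below does not count this.

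**4. Dilution**

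Let d be the true between-arm difference in change at 3 months, c the change in the comparison arm, and f_I and f_C the shares of 3-month values that predate the intervention in each arm. Assume that reuse is unrelated to a participant's own response. Reused values contribute no change, so:

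- intervention arm: expected change = (1 - f_I)(c + d)
- comparison arm: expected change = (1 - f_C)c
- difference = (1 - f_I)d + (f_C - f_I)c

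With the same share f in both arms this reduces to (1 - f)d.

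| f | Share of the true effect retained |
|---|---|
| 0% | 100% |
| 10% | 90% |
| 25% | 75% |
| 50% | 50% |

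The article does not give f, so these rows are a range and not an estimate.

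**The case against.** **It is only a permission.** The footnote allows early values; it does not say that any will be used. How many there are depends on routine testing dates and on whether a newer value exists. With routine tests every three months or more often, and the latest value always taken, no 3-month value need come from before the baseline visit. This stands. A reader might infer that part of the 3-month comparison certainly holds no follow-up data; the article shows only that it may.

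**A single figure cannot be given.** A reader might reason that 1 of the 4 accepted months lies before baseline, so the effect shrinks by 25%. That assumes evenly spread dates, and also that every 3-month value comes from the record. If a share s comes from the record, even spread gives f = 0.25 x s; for s = 40% this is 10%. Neither s nor the spread is stated. The true share could also be higher than this reasoning gives, because reused baseline-visit draws are not counted separately in it.

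**Further inferences lack a source.** At least six months of attendance before entry makes earlier results plausible, but the article gives no HbA1c testing frequency, so it does not show that they are common. Nor does it say that testing differs between centres. Table 1 sets the same rule for both arms, so a bias that differs by arm is possible in the formula above but not shown.

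**The wording is loose.** Missing from the record might mean that no value exists for that time point, which would trigger a draw. But the second condition has a purpose only if values up to 4 months old are accepted for the visit, so this reading does not close the gap.

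**Use of routine data is deliberate.** The trial is meant to sit within routine diabetes care, and record values save work. That supports record values in general. It does not support a window longer than the interval being measured.

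**The weight is limited.** The point concerns one biomarker among several secondary outcomes, at the interim time point, and the expected direction is to understate an early effect. This stands and bounds the point.

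**Conclusion.** The point holds as a flaw in a stated measurement rule. A 4-month look-back at a visit 3 months after baseline admits results from the month before baseline and results drawn at the baseline visit, and nothing else in the article excludes them. Where one result serves both visits, the change is zero by construction.

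The likely consequence is dilution of the 3-month HbA1c difference towards no effect, with about (1 - f) of it remaining. This rests on an equal share f in both arms and on reuse that is unrelated to response. The size of f is unknown from the document.

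The 12-month HbA1c, for which a fresh sample is mandatory, is not affected. Nor is the primary physical activity outcome. The rule should be changed, but no conclusion on the primary objective depends on it.

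**What to change.** Change footnote a so that HbA1c at 3 months is measured in every participant, as is already mandatory at 12 months, using the fasting venous sample that Table 1 schedules for lipids at that visit in both arms. This reduces the overlap to zero. Record substitution at baseline may remain as far as this point is concerned.

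If record values must still be allowed at 3 months, the minimum is to accept one only when it was taken after baseline and close to the 3-month visit, within a window that the investigators prespecify, and to draw blood otherwise. The sample date of each accepted value then has to be recorded.

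The cost of the preferred change is one reworded footnote and some additional HbA1c assays. Because the lipid sample is already planned, no extra visit or blood draw is needed.
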